### Eligibility criteria {10}

Inclusion criteria are as follows:Age 40 years or older.Ongoing LFOT, prescribed for at least 15 h per day, and for a minimum of 28 days as registered in Swedevox.COPD or ILD as the main underlying reason for LFOT.Oxygen concentrator as a stationary oxygen source in the home including night-time.Body mass index (BMI) < 35 kg/m^2^ (to reduce potential confounding related to obesity-associated respiratory issues and sleep apnea).

Exclusion criteria are as follows:Current or previous treatment with home HFOT.Current treatment with home mechanical ventilation.Current treatment with home continuous positive airway pressure (CPAP).Hospitalised during the last 2 weeks.Current smoking or contact with flames.Self-reported average use of the LFOT < 15 h per day (24 h).PaCO2 (breathing air at rest) > 8 kPa.Strong clinical suspicion of obstructive sleep apnoea or obesity hypoventilation syndrome (as judged by the responsible staff).Inability to participate in the study procedures (as judged by the staff).Not eligible for continuing LFOT due to other reason (as judged by the staff).Expected survival less than 3 months (as judged by the staff).

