### Sample size {14}

The sample size will be 270 randomised people with COPD and with data on the primary outcome. This sample size was determined to provide 80% power to detect a clinically meaningful between-group difference in the primary outcome (time to first hospitalisation or death from all causes during 1 year) of hazard ratio 0.67 in people with COPD, using a two-sided test, assuming equal allocation between the treatment groups, a 1-year rate of the primary outcome of 0.74 in the target population in the Swedevox registry; and a false positive rate (alpha) of 0.05 [33].

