Data from the National Patient Registry from 1 January 1997 to end of trial for all in and outpatient care will be used to assess comorbidities at baseline, and time to, rate, and reason of hospitalisation and incident conditions and procedures during follow-up. Data from the Drug Registry on all dispensed outpatient prescriptions will be obtained from 1 year before the date of randomisation until the end of follow-up in the study. Data from the Intensive Care Registry on length of stay, procedures, treatments, complications, and death will be obtained to assess ICU care from 365 days before randomisation throughout follow-up. Data from the Cause of Death Register will be used to assess the date, place, whether autopsy was performed, and the causes of death throughout follow-up.

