## Statistical methods

### Statistical methods for primary and secondary outcomes {20a}

A detailed statistical analysis plan (SAP) will be established and published in collaboration with a biostatistician before the lock of the database for the primary analysis and before performing each secondary analysis.

The population for efficacy analyses is defined as all randomised people who did not withdraw their consent to be included in the outcome analyses (ITT population). The population for safety analyses is defined as all randomised people who started their randomised treatment (safety population). All analyses will be performed primarily by randomised treatment group (ITT) and secondarily by treatment used (PP).

Data will be summarised using mean with standard deviation and median with range and interquartile range for continuous variables with normal and skewed distributions, respectively. Categorical variables will be expressed as frequencies and percentages. Differences between groups will be analysed using Student’s *t*-tests (for normally distributed continuous outcomes), chi2 tests (for dichotomous outcomes), and Wilcoxon’s rank sum test (for ordinal and non-normally distributed data).

Outcomes will be compared between the treatment groups using multivariable regression models, expressed as point estimates with 95% confidence intervals. The primary outcome will be analysed using Cox proportional-hazards regression. Secondary outcomes will be analysed using appropriate statistical methods: logistic regression for categorical outcomes, Cox regression for standard survival analysis, Fine–Gray regression for competing risk scenarios, and linear regression for continuous outcomes, ensuring robust and context-appropriate analysis. Mixed regression models with random effects will be used to analyse outcomes measured in the same individual at several time points to account for repeated measurements. The outcome analyses will be adjusted for age and sex, the stratification variables, number of hospitalisations during the 12 months before baseline, and time from starting LFOT in Swedevox. Statistical significance will be defined as a two-sided *p*-value < 0.05.

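### The covariate list leaves out two prognostic baseline variables that the trial will obtain from registries (comorbidity and prior-year dispensings): a missed gain in efficiency, not an error

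*Protocol article*

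**What the plan says.** All places are in the Protocol article.

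- **Statistical methods {20a}** specifies Cox regression for the primary outcome and one adjustment set for all outcomes: "The outcome analyses will be adjusted for age and sex, the stratification variables, number of hospitalisations during the 12 months before baseline", followed by time since LFOT was started. A detailed SAP is to be published before database lock.
- **Plans for assessment and collection of outcomes {18a}** commits the trial to National Patient Registry data that "for all in and outpatient care will be used to assess comorbidities at baseline". From the Drug Registry, "all dispensed outpatient prescriptions will be obtained from 1 year before the date of randomisation". Neither appears in the adjustment set.
- **Trial design {8}** names the stratification variables as underlying diagnosis (COPD or ILD) and study centre.
- **Outcomes {12}** restricts the primary outcome to COPD. It defines time to first exacerbation by dispensed antibiotics and/or oral corticosteroids, among other events.
- **Eligibility criteria {10}** mentions arterial carbon dioxide only as an exclusion threshold: "PaCO2 (breathing air at rest) > 8 kPa".
- **Sample size {14}** gives the planning figures: 270 participants with outcome data, 80% power, a two-sided test, "a false positive rate (alpha) of 0.05", a hazard ratio of 0.67, and "a 1-year rate of the primary outcome of 0.74 in the target population in the Swedevox registry".

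**The concern.** Adjusting a Cox model for baseline variables that predict the outcome usually raises the power of the treatment comparison without recruiting anyone else. Comorbidity and recent exacerbation treatment are natural candidates in people on long-term oxygen, and the trial is obtaining both.

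Two features of the plan sharpen the point. First, the list does less for the primary analysis than it appears to. Diagnosis is constant in a COPD-only population, so age, sex, centre, prior hospitalisations and time on LFOT remain. Second, the plan adjusts a hospitalisation endpoint for earlier hospitalisations, but it does not adjust an exacerbation endpoint for the earlier count of the dispensings that help define it. That asymmetry is visible in the text and needs no assumed effect size.

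At stake is some precision in the one confirmatory comparison, which is planned with little power to spare.

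**Working it through.** **1. The plan's own figure.** Inputs from Sample size {14}: hazard ratio 0.67, two-sided alpha 0.05, 80% power, 1:1 allocation, 1-year event rate 0.74.

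- Schoenfeld: events = 4(1.960 + 0.842)² / (ln 0.67)² = 31.40 / 0.1604 = 195.8, so 196; 196 / 0.74 gives 265 participants.
- Freedman: events = (1.960 + 0.842)² × (1.67 / 0.33)² = 7.849 × 25.61 = 201.0, rounded up to 202; 202 / 0.74 gives 273 participants.
- Power at 270: 270 × 0.74 = 199.8 events; √199.8 × 0.4005 / 2 − 1.960 = 0.870, which is 80.8% power.

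The stated 270 lies between the two answers and reproduces. No covariates enter this calculation.

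**2. What adjustment could add.** The documents do not give the prognostic strength of the two variables after the listed covariates, so it is assumed. They are represented by one standard normal score, independent of the listed covariates, with log-hazard effect s per SD. Trials of 270 were simulated with 1:1 allocation, exponential times, censoring at 1 year and an overall event rate of 0.74 (about 200 events). Each was analysed by Cox regression with and without the score.

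The section does not say whether 0.67 is covariate-conditional or marginal, so both readings were run.

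*Reading A: 0.67 is the conditional hazard ratio* (3,000 trials per row; Monte Carlo standard error at 80% power is √(0.8 × 0.2 / 3000), about 0.7 points).

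| s per SD | HR, score omitted | HR, score included | Power, omitted | Power, included | Gain (points) |
|---|---|---|---|---|---|
| 0 | 0.669 | 0.669 | 80.9% | 80.5% | none |
| 0.2 | 0.673 | 0.667 | 79.0% | 81.0% | 2.0 |
| 0.3 | 0.682 | 0.669 | 77.3% | 80.5% | 3.2 |
| 0.4 | 0.691 | 0.669 | 74.5% | 81.4% | 6.9 |
| 0.5 | 0.702 | 0.670 | 70.8% | 80.5% | 9.7 |

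*Reading B: 0.67 is the marginal hazard ratio, seen with the score omitted* (2,000 trials per row; standard error about 0.9 points).

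| s per SD | Implied conditional HR | Power, omitted | Power, included |
|---|---|---|---|
| 0.3 | 0.654 | 80.8% | 83.5% |
| 0.5 | 0.634 | 81.0% | 89.2% |

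The simulation compares treatment alone with treatment plus the score. The listed covariates are not modelled, so s has to be read as what remains after them.

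**3. Room in the model.** With ten centres entered as nine indicators, the covariate terms are age 1, sex 1, centre 9, prior hospitalisations 1 and time on LFOT 1, which makes 13. Two more make 15. At 200 events that is 200 / 15 = 13.3 events per covariate term.

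If 0.74 described the control arm only, the treated risk would be 1 − 0.26^0.67 = 0.594 and the average risk 0.667. That gives 180 events and 180 / 15 = 12 events per term.

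**The case against.** The case against is substantial, and most of it stands.

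- **The planned model is valid.** It already contains prior-year hospitalisations, the baseline counterpart of the endpoint's main component. A trial need not adjust for everything it collects, and the comorbidity data have a stated descriptive use.
- **Residual strength is unknown.** Comorbidity and exacerbation treatment probably overlap with prior hospitalisations. Nothing in the documents supports 0.4 or 0.5 per SD over 0.2 or zero.
- **A reader might infer that the plan loses power or biases the hazard ratio towards 1.** The documents do not support that. The sample size reproduces without covariates, and if 0.67 is marginal the planned power is intact. The movement from 0.67 towards 0.70 in Reading A is non-collapsibility: marginal and conditional hazard ratios are different estimands. Chance imbalance between arms is already reflected in the confidence interval.
- **A reader might also infer that PaCO2 is another variable in hand.** The article gives only an exclusion threshold and does not say that the value is recorded for analysis.
- **The SAP is still to come and could add covariates.** That is true, but the article states a definite list and does not leave the choice open. An extension made and dated before lock is easier to defend than a later one.

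The objection does not remove the documentary point: two relevant baseline variables are to be obtained and are not listed, and the exacerbation outcomes are not adjusted for their own prior-year component.

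**Conclusion.** The point holds as a missed efficiency. The primary analysis is sound and its 80% power is not contradicted.

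The gain depends on an assumption that the documents cannot settle. For 0.2 to 0.5 log-hazard per SD beyond the listed covariates, it is about 2 to 10 points of power if 0.67 is conditional. If 0.67 is marginal, power rises from about 81% to 83.5–89% for 0.3 to 0.5 per SD. With no residual information, power is essentially unchanged. The lower part of the range is the safer expectation, because prior hospitalisations may already carry some of the same information.

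The dispensing count is the stronger of the two candidates, since for time to first exacerbation it is the prior-year value of part of the outcome itself. PaCO2 is not part of the conclusion unless its value proves to be recorded.

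**What to change.** Before database lock, extend the covariate list in Statistical methods {20a}, and carry it into the SAP:

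1. Add to the primary Cox model a comorbidity count from the National Patient Registry, with the conditions and look-back period defined in advance.
2. Add the number of antibiotic and oral corticosteroid dispensings in the year before randomisation from the Drug Registry, with a rule for what counts as one dispensing.
3. Use the dispensing count as a covariate for the exacerbation outcomes as well.
4. Add PaCO2 only if the eligibility value is recorded for analysis. Missing values would then fall under the multiple imputation already planned.

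The cost is two parameters beyond roughly 13 covariate terms, against about 180 to 200 events, and the work of defining the two counts. No further participants are needed, and items 1 to 3 need no new data. Because the additions are prespecified baseline variables, they do not bias the test.

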### Outcomes {12}

The primary outcome is time to first hospitalisation or death from all causes during 1 year after randomisation in people with COPD (at 1 year, assessed using nationwide registries).

Secondary outcomes are as follows:Time to first all-cause hospitalisation or all-cause death in people with ILD (at 1 year after randomisation, assessed using nationwide registries).Rate of hospitalisations or death from all causes (at 1 year).Hospitalisation rate from all causes (1-year and long-term).Hospitalisation rate from respiratory disease (1-year and long-term).Hospitalisation rate from cardiovascular disease (1-year and long-term).Number of hospitalised days (all-cause/respiratory disease/cardiovascular disease) (at 1 year and long-term).Number of admissions to intensive care unit (ICU) (at 1 year and long-term).Number of days in ICU care (at 1 year and long-term).The mortality rate from all causes (at 1 year and long-term).The mortality rate from respiratory disease (at 1 year and long term). The mortality rate from cardiovascular disease (at 1 year and long-term).Time to first exacerbation after randomisation, defined as time to first dispensed antibiotics and/or oral corticosteroids, emergency department visit, or hospitalisation for exacerbation (at 1 year).Number of exacerbations of all severity (at 1 year).Incidence of cardiovascular disease (at 1 year and long-term).Need for home mechanical ventilation (at 1 year and long-term).Rate of LFOT withdrawal (at 1 year and long-term).Safety and tolerability (adverse events at 3 and 12 months).Cost-effectiveness (at 1 year and long-term).HRQL (at 3 and 12 months).Symptoms (dyspnea, cough, phlegm, upper airway symptoms, fatigue, including nighttime symptoms, sleep) (at 3 and 12 months).Factors associated with the net clinical benefit of the HFOT, including the daily usage time.Patients’ perceptions of oxygen therapy and related factors.Adverse events as safety endpoints.

The secondary outcomes will be evaluated in the following populations: (1) people with COPD; (2) people with ILD; and (3) all people. All analyses will be performed primarily by randomised treatment group (intention to treat; ITT), and secondarily by treatment used (per protocol; PP).

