## Data collection and management

### Plans for assessment and collection of outcomes {18a}

Outcome data will be obtained from patient questionnaires at baseline, 3 and 12 months, from Swedevox, from trial specific data entered in the eCRF by the PIs, and from national registries. In centres using the remote home-monitoring system AirView, data on HFOT utilisation will be used.

The questionnaires will include questions on oxygen and HFOT usage, patient preference for continuing the treatment, utilisation of primary care and domestic service, adverse events, and the number of exacerbations since the start of the trial. Symptoms included in the questionnaires are breathlessness using a modified Dyspnoea Exertion Scale (DES) [34] and the Dyspnoea-12 questionnaire [35, 36], cough and phlegm assessed by relevant items in the COPD Assessment Test (CAT) [37], sleep complaints using a modified Basic Nordic Sleep Questionnaire (BNSQ) [38], nasal symptoms, and subjective perception of change in health status assessed with a modified Global Impression of Change (GIC) scale [39]. Physical activity is reported for the previous month using a modified Grimby activity questionnaire [40, 41], and HRQL is evaluated using the CAT [37] and EuroQol Five Dimensions Five Levels (EQ5D-5D-5L) [42].

Data from Swedevox will be used for characterising the people and their oxygen treatment, and for assessment of rate and reason of LFOT withdrawal during follow-up. The ventilator arm of the Swedevox registry will be used to assess the incidence of long-term home mechanical ventilator usage.

If applicable, data on HFOT utilisation will be collected from centres using Airview at 1 week, 3 and 12 months on: average usage time, daytime and nighttime use, days of use, and days of use ≥ 4 h/24 h. Data on oxygen flow and HFOT settings will be collected from staff-reported questionnaires at 3 and 12 months.

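### The two exacerbation outcomes are not adjusted for prior-year exacerbations, although the planned registry extracts can supply them: a modest, avoidable loss of precision

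*Protocol article*

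**What the plan says.** All references are to the protocol article.

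- **Statistical methods for primary and secondary outcomes {20a}** states one covariate list for the outcome analyses: age, sex, the stratification variables, "number of hospitalisations during the 12 months before baseline, and time from starting LFOT in Swedevox". The list is not limited to the primary outcome. The same section promises a detailed SAP before database lock and before each secondary analysis.
- **Outcomes {12}** has two exacerbation outcomes, both secondary. The first is "Time to first exacerbation after randomisation, defined as time to first dispensed antibiotics and/or oral corticosteroids", an emergency department visit, or admission for exacerbation. The second is the one-year number of exacerbations of any severity, with no data source named.
- **Plans for assessment and collection of outcomes {18a}** supplies the baseline data: "Data from the Drug Registry on all dispensed outpatient prescriptions will be obtained from 1 year before the date of randomisation", and "Data from the National Patient Registry from 1 January 1997 to end of trial for all in and outpatient care". The same section has patients report "the number of exacerbations since the start of the trial" by questionnaire.

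**The concern.** An outcome's own value before randomisation is usually among its best predictors. The stated list follows that logic for hospitalisation, by including prior-year hospitalisations, but not for exacerbations. Prior admissions capture only those past exacerbations that reached hospital. As no cause is specified, they also count admissions for other reasons. Drug-treated episodes and emergency visits in the previous year are left out, although they are part of the time-to-first definition and the data are already planned.

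What is at stake is power and precision for these two outcomes. The sample size was set for the primary outcome, and the article claims no power for exacerbations. The Background nevertheless cites fewer exacerbations as a reported effect of HFOT in the earlier Danish and Japanese studies, so readers will look at these results.

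**Working it through.** **1. The plan's own figure.** Inputs from Sample size {14}: HR 0.67, 80% power, two-sided alpha 0.05, 1:1 allocation, one-year event proportion 0.74 (taken as the average over both arms).

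- Schoenfeld: events = 4(1.960 + 0.842)² / (ln 0.67)² = 196; 196 / 0.74 = 265.
- Freedman: events = (1.67 / 0.33)² × (1.960 + 0.842)², rounded up to 202; 202 / 0.74 = 273.
- Power with 270 × 0.74 = 199.8 events: 80.8%.

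The stated 270 reproduces and does not involve the exacerbation outcomes.

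**2. Can the covariate be built?** Dispensed drugs are available for exactly the preceding year. Admissions are in the National Patient Registry extract. Emergency visits are assumed to be there too, since no other named registry would hold them. The time-to-first definition can then be applied to the 365 days before randomisation.

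**3. Linear approximation.** Let y be follow-up exacerbations, x prior exacerbations and h prior hospitalisations. The partial correlation of y and x given h is

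r = (r_yx − r_yh·r_xh) / √[(1 − r_yh²)(1 − r_xh²)].

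The share of variance removed is r², and the gain in effective sample size is 1/(1 − r²) − 1. With r_yh = 0.3 and r_xh = 0.6 (assumed):

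| r_yx | partial r | variance removed | gain |
|---|---|---|---|
| 0.3 | 0.157 | 2.5% | 2.5% |
| 0.4 | 0.288 | 8.3% | 9.1% |
| 0.5 | 0.419 | 17.6% | 21.3% |

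A gain of 10% needs a partial r of about 0.30, and 29% needs about 0.47. Letting r_yx run over 0.3–0.5, r_yh over 0.2–0.4 and r_xh over 0.4–0.8 gives 0–33% of variance removed. The top (a 50% gain) needs prior admissions that nearly duplicate prior exacerbations (0.8) yet barely predict later ones (0.2).

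**4. Simulation of time to first exacerbation (Cox).** Assumed: n = 270, conditional HR 0.67 (borrowed from the primary outcome), mean 2 exacerbations a year, death hazard 0.35 a year. Both models contain arm and log(1 + prior hospitalisations); one adds log(1 + prior exacerbations). Gain = squared ratio of mean z. The stable row uses gamma-distributed rates and 500 replicates; the 0.85 row uses log-normal rates, non-exacerbation admissions added to the prior count, and 600 replicates. Where two figures are joined by a dash, they span the dispersions.

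| Year-to-year stability of personal rate | 30% hospitalised, dispersion 0.5 / 1.0 / 1.5 | 50% hospitalised |
|---|---|---|
| Perfect | 10% / 23% / 29% | 7–14% |
| Correlation 0.85 | 7% / 12% / 15% | 5% / 6% / 12% |
| Correlation 0.7 | 4–9% | 3–6% |
| Correlation 0.5 | 2–6% | 1–3% |

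Repeats of the perfect-stability row at 30% hospitalised gave 11% / 22% / 31% (800 replicates) and, with log-normal rates, 8% / 22% / 24% (600 replicates). In the stable row, power rose from 60% to 65%, 48% to 57% and 39% to 51%. The Monte Carlo SE of each power is about √(0.25/500) = 2 points. Rejection under no effect was 6.0% and 5.4% (SE about 1 point), consistent with 5%.

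**5. Simulation of the count (quasi-Poisson).** Assumed: mean 1.5 or 2.5 a year, dispersion 0.4 or 0.8, log-rate correlation 0.5, 0.7 or 0.9, 30% or 60% hospitalised; 24 scenarios of 300 runs. Gains run from 1% to 19%, and 20 of the 24 are below 10%. The four at or above 10% all have 30% hospitalised and a correlation of 0.7 or 0.9.

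The gain is positive in every scenario reported. The simulations omit age, sex, centre and time since LFOT began from both models. These could absorb some of the same variation, so the gains may be slightly overstated.

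**The case against.** - **The adjustment is already reasonable.** A reader might infer that exacerbations are adjusted for prior hospitalisations alone. They are not: age, sex, the stratification variables and time since LFOT began are also in the model. Prior admissions also carry part of the exacerbation history. This stands, and it is why the increment is often small.
- **The size is not documented.** A reader might take 10–29% of the effective sample as lost. That range appears only if each person's rate is identical in both years and 30% of exacerbations lead to admission. The article gives neither figure. Eligibility needs only 28 days of LFOT, so for some participants most of the prior year precedes oxygen treatment, which argues against perfect stability. In a population where 74% are hospitalised or dead within a year, a higher hospitalised share is plausible. This stands.
- **Nothing is invalid.** A reader might infer bias. Omitting a prognostic covariate in a randomised comparison does not invalidate the test. The adjusted HR moved, for example from 0.73 to 0.70 against a conditional 0.67. That is non-collapsibility: the two models estimate different hazard ratios. This stands.
- **The SAP may add the covariate.** It may. But the article states a list for the outcome analyses, so the point concerns a stated choice that fits two named outcomes poorly. A later addition would depart from the published list unless fixed in advance. This objection stands only in part.
- **The count may come from questionnaires.** The article names no source for it and does collect a self-reported number. For that outcome the matching baseline applies only if the count is registry-derived. This stands.

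**Conclusion.** The point holds as a matter of efficiency. The stated covariate list gives the two exacerbation outcomes no baseline counterpart, although planned extracts can provide one. The gain from adding it is roughly 1–29% in effective sample size, depending on assumed dispersion, hospitalised share and year-to-year stability. It is often below 10% unless personal rates are very stable. None of these inputs is in the article, so no single figure should be quoted as fact. Two secondary outcomes are affected. The validity of the randomised comparison, the primary outcome and the 270 participants are not.

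**What to change.** In the Statistical methods section, add a sentence for time to first exacerbation and, where it is derived from registries, for the number of exacerbations. These models should also include log(1 + number of exacerbations in the 365 days before randomisation), derived from the Drug and National Patient Registries with the outcome definition and the same rule for counting separate episodes. Keep the existing covariates, including prior-year hospitalisations. State the source of the exacerbation count so that it is clear whether the addition applies to it. Fix all of this before database lock.

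The cost is one derived variable from data already planned, one line of text and one extra model parameter, with no added burden on participants.
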